**Abstract/Summary:**

BACKGROUND: Palonosetron is a second generation serotonin antagonist usually used in a ﬁxed dose of 75 mcg for the prophylaxis of postoperative nausea and vomiting. Although there are a few trials evaluating bodyweight-adjusted doses of palonosetron, the ideal dose for obese patients has not yet been investigated. The aim of this study is to evaluate if the use of bodyweight-adjusted doses of palonosetron (1mcg / kg) is more effective than a fixed dose (75mcg) on preventing postoperative nausea and vomiting in female patients with a body mass index equal to or above 30 kg /m2 whom have undergone breast surgery

METHODS: A prospective, randomized double-blind trial will be conducted at the National Cancer Institute (INCA - HCIII), in Rio de Janeiro, Brazil. Eligible patients are female aged between 18-70 years of age with an ASA physical status of one to three, with body mass index equal to or greater than 30 kg / m2, scheduled to undergo elective breast surgery. Forty patients will be randomized to receive a bodyweight-adjusted dose of 1mcg/kg of palonosetron (group I - GI) and 40 patients will receive a fix dose of 75 μg of palonosetron (group II - GII). Patients will be assessed over 4 time periods: 0-1h, 1-6 h, 6-24 h and 24-48 h after surgery. After discharge, all patients will be contacted by telephone at regular intervals to record the episodes of nausea and vomiting as well as analgesic and antiemetic requirements. The primary outcome measure will include the number of emetic episodes, the incidence of nausea, the need for rescue antiemetics and the analgesic requirement over 48h. The secondary outcome will be to evaluate the frequency of polymorphism of the 5-HT3 receptors and their correlation with the antiemetic effect and adverse effects.

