**Aims & Objectives**

Our hypothesis for this study is that the use of bodyweight-adjusted doses of palonosetron (1mcg / kg) is more effective than a fixed dose (75mcg) for preventing postoperative nausea and vomiting in female patients with a body mass index equal to or above 30 kg / m2 whom have undergone breast surgery.

Primary objectives:

1. To determine the frequency of individual episodes of nausea in the periods of 1, 6, 24 and 48 hours postoperatively
2. To determine the frequency of individual episodes of vomiting in the periods of 1, 6, 24 and 48 hours postoperatively
3. Compare need of antiemetic rescue medication during the periods of 1, 6, 24 and 48 hours postoperatively
4. Determine the number of patients who had complete antiemetic response (absence of nausea, vomiting and need for rescue medication).

Secondary objectives: To evaluate the frequency of polymorphism of the 5-HT3 receptors and their correlation with the antiemetic effect and adverse effects

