All patients will receive premedication with midazolam. Intraoperative monitoring included electrocardiography, blood pressure measurement, peripheral oxygen saturation (SpO2), and end-tidal CO2 tension (ETco2). General anesthesia was induced using 1,5 mg/kg of propofol, 3 μg/kg of fentanyl, 1,5 mg/kg of lidocaine and 0.3 mg/kg of rocuronium. Then the insertion of laryngeal mask will be performed and the pulmonary ventilation will be maintained with 6 ml/kg of ideal-weight and maximum peak pressure 25 cmH2O. The anesthesia will be maintained with sevoflurane in 50% oxygen/air. Sevoflurane concentration was adjusted to ensure an equal depth of anesthesia during surgery as assessed by the bispectral index (BIS; BIS A-1050 Monitor, Aspect Medical Systems, Newton, MA, USA), which will be held between 40-60. Remifentanil will be administered for supplemental intraoperative analgesia and its dose will be adjusted to maintain blood pressure and heart rate within 20% of baseline values. At the end of surgery, residual neuromuscular blockade will be reversed with 2mg/kg of Sugammadex and the laryngeal mask will be removed. Patients will stay on the postanesthetic care unit for at least 1 hour before going to the ward. In the postoperative recovery room, the haemodynamic variables along with postoperative complications such as shivering, hypotension, dizziness, constipation or any other adverse reaction to the drug will be recorded by a blinded observer. After surgery, rescue medication will be intravenous metoclopramide (10 mg) for more than one episodes of nausea or vomiting.

All episodes of nausea and vomiting will be recorded for 48h. Patients will be assessed over 3 time periods: 0-6 h, 6-26 h and 24-48 h after surgery. After discharge, all patients will be contacted by telephone at regular intervals to record the episodes of nausea and vomiting as well as analgesic and antiemetic requirements. The primary outcome measure will include the number of emetic episodes, the incidence of nausea, the need for rescue antiemetics and the analgesic requirement after 48h. Nausea is deﬁned as a subjective unpleasant sensation associated with the urge to vomit without expulsion of gastric content and vomiting is deﬁned as the forceful expulsion of gastric contents trough the mouth.

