The secondary outcome will be to evaluate the frequency of polymorphism of the 5-HT3 receptors and their correlation with the antiemetic effect and adverse effects. The patients will have cell samples of the oral cavity, collected through smear. The collected material will be placed in a tube and then will be stored at freezer. Then, it will be analyzed in the laboratory of Clinical Research Unit at the Federal Fluminense University (UFF). After extracting the DNA from the samples using a DNA purification kit, a polymerase chain reaction (PCR) will be performed for analysis of single nucleotide polymorphisms. Biological samples will be discarded at the end of the analysis.

Sample size was calculated with reference to the results of a study comparing weight-adjusted doses of palonosetron for prevention of PONV in laparoscopic gynaecological surgery in no-obese patients. For a P value of 0.05 and a power of 0.8, a minimum of 36 per dose group was required. To allow for possible dropouts, the aim was to recruit 40 patients in each group.

GraphPad Prism 4.0® (GraphPad Softwares Inc., San Diego, CA, USA) will be used for statistical analysis. The Wilcoxon signed rank 2x2 test will be use to ensure that data will be normally distributed. Patient characteristics and intra- and post-operative variables will be analysed by Unpaired Student´s t-test. Proportions will be compared using x^2^ square or Fisher’s exact test. A P value < 0.05 is considered statistically significant.

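### The primary outcome is stated inconsistently: complete response is primary only in the Aims, analgesic requirement only in the Abstract and Methods, and nothing says which governs

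*Protocol*

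**What the plan says.** Aims & Objectives gives four primary objectives. Three concern nausea episodes, vomiting episodes and rescue antiemetic use, each at 1, 6, 24 and 48 hours. The nausea objective reads "To determine the frequency of individual episodes of nausea in the periods of 1, 6, 24 and 48 hours postoperatively". The fourth reads "Determine the number of patients who had complete antiemetic response (absence of nausea, vomiting and need for rescue medication", and it has no time window. Analgesic use is in no objective, primary or secondary.

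The Abstract/Summary gives its primary outcome as a list of four items: "the number of emetic episodes, the incidence of nausea, the need for rescue antiemetics and the analgesic requirement over 48h". Methods repeats the sentence with one changed word at the end: "the number of emetic episodes, the incidence of nausea, the need for rescue antiemetics and the analgesic requirement after 48h". Neither sentence mentions complete response.

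The sample-size text in Methods says "For a P value of 0.05 and a power of 0.8, a minimum of 36 per dose group was required", by reference to an outside study. It names no endpoint, rates or effect size. The analysis text in Methods sends proportions to a chi-square or Fisher's exact test and post-operative variables to an unpaired t-test, with one significance threshold of 0.05.

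**The concern.** The primary outcome decides whether the trial supports its hypothesis, which is better prevention of nausea and vomiting with the weight-adjusted dose. Two analysts working from different sections would report different primary results. One would include complete response, which matches the hypothesis directly. The other would leave it out and could report a difference in analgesic requirement as a primary finding, although that outcome does not measure prevention of nausea and vomiting. Because the items are unranked, the choice between them could be made once the results are known.

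This is not a detail left to a statistical analysis plan. The protocol does fix its primary outcome, in three places that conflict, so an analysis plan would have to overrule at least one of them.

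**Working it through.** **1. The three statements side by side**

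| Item | Aims & Objectives | Abstract/Summary | Methods |
|---|---|---|---|
| Nausea | count of episodes, four time points | incidence | incidence |
| Vomiting | count of episodes, four time points | number of emetic episodes | number of emetic episodes |
| Rescue antiemetic | need, four time points | need | need |
| Complete response | primary, no window | absent | absent |
| Analgesic requirement | absent | primary, over 48 h | primary, after 48 h |

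Three items are shared in substance, and each side has one that the other lacks: 3 + 1 + 1 = 5 distinct items with a claim to be primary.

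**2. Does the nausea wording matter?** Under the analysis text in Methods, an incidence is a proportion and goes to chi-square or Fisher's exact test. A count of episodes is most naturally a post-operative variable and goes to the t-test. So the wording changes the test as well as the label.

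**3. Can the sample size show which item governs?** The plan's 40 per group follows from 36 if 10% dropout is assumed (the rate is not stated): 36 / (1 − 0.10) = 40. The 36 itself cannot be reproduced, because no rates, effect or endpoint are given. What it could detect, assuming a two-sided 0.05 (sidedness is not stated) and power 0.80, is:

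- For a mean: standardised difference = (1.960 + 0.842) × √(2/36) = 0.66.
- For a proportion, with n = [1.960·√(2p̄(1−p̄)) + 0.842·√(p₁(1−p₁) + p₂(1−p₂))]² / (p₁−p₂)²: taking p₁ = 0.50 and p₂ = 0.191 gives p̄ = 0.3455 and n = (1.318 + 0.535)² / 0.309² ≈ 36.
- Over assumed higher rates from 20% to 80%, the detectable difference runs from about 20 to 32 percentage points (for example 50% against 19%, or 60% against 28%).

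The figure of 36 is therefore compatible with a count, an incidence or complete response. It does not identify the endpoint.

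**4. Size of the freedom to choose.** If k items are each tested at 0.05 and are independent, the chance of at least one false positive is 1 − 0.95^k.

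- Either four-item list: 1 − 0.95⁴ = 0.185.
- All five distinct items: 1 − 0.95⁵ = 0.226.

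Nausea, vomiting, rescue and complete response are plainly correlated, so these figures illustrate the upper end and are not estimates.

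**The case against.** The strongest reply is that the lists are close. Three items are common to both, complete response is built from exactly those three, and the outcome sentences say the measure will include the items, which is not strictly exclusive. All of that stands as far as the data go: complete response can be derived under any of the three sections, and since Methods records every episode, nausea can be reported either way. It does not settle which result is primary, and it does not explain an analgesic outcome that answers to no objective.

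Three stronger readings may tempt a reader, and the documents support none of them.

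- *That analgesic requirement after 48 h falls outside the observation period and leaves no data.* The Abstract has the same sentence with over in place of after. Methods ties its 48-hour recording limit to nausea and vomiting episodes, and separately says that the telephone calls after discharge record analgesic requirements. The phrase may also belong to all four items. It is evidently a slip.
- *That complete response would be lost.* Its components are collected; what is unclear is its status.
- *That only complete response is protected from the effect of rescue metoclopramide.* Methods gives rescue after more than one episode, so a patient rescued under that rule has already failed complete response. Nausea incidence over the whole 0-48 h shares the same protection. Rescue affects episode counts and later periods, not every listed outcome.

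It is also fair to say that the contradiction alone does not force complete response to be the sole primary. That is a recommendation, argued under the fix.

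**Conclusion.** The contradiction holds and should be corrected, because it concerns which result decides the trial. It consists of one mismatched item on each side (complete response and analgesic requirement), a change in how nausea is measured that carries over to the test, and no ranking or sample-size link to resolve either. The difference between over and after 48 h is editorial and adds no weight.

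The textual finding needs no assumption. The error rates of about 18.5% and 22.6% assume that every listed item is tested at 0.05, that the tests are independent, and that any one of them could be taken as decisive. An analysis plan that is not shown might set an order of testing, but it could not agree with all three sections as they now stand.

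**What to change.** Name one primary outcome and word it identically in the Abstract/Summary, Aims & Objectives and Methods. Complete response over 0-48 h is the best-supported choice: it is already defined and primary in the Aims, it matches the hypothesis, and it needs no new data. The window has to be added, because the Aims give none. The assessment periods listed in the Abstract and in Methods differ, but both end at 48 h, so the window fits either.

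Make nausea, emetic episodes, rescue antiemetic use and analgesic requirement over 0-48 h secondary, and say whether nausea is an incidence or a count. Change after to over in the Methods sentence. In the sample-size paragraph, state the endpoint and the rates on which the 36 per group rests.

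The cost is wording in those sections plus one check: the basis of the sample size must be compared with the chosen endpoint, and the 36 may need to be recalculated if it was derived for another. Some items now called primary become secondary.

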### Methods

A prospective, randomized double-blind trial will be conducted at the National Cancer Institute (INCA - HCIII), in Rio de Janeiro, Brazil. All patients will be provided with written informed consent form prior to study enrolment. Eligible patients are female aged between 18-70 years of age with an ASA physical status of one to three, with body mass index equal to or greater than 30 kg / m2, scheduled to undergo elective breast surgery. The exclusion criteria are: patients who had received chemotherapy within 4 weeks, patients who have undergone emergency surgery, with known history of vomiting within 24 hours; a known hypersensitivity to other 5-HTantagonists, patients who received any antiemetic, corticosteroid, or other drug with antiemetic effect, smokers and patients with a history of alcoholism.

Using computer-generated random numbers, the patients will be assigned into one of the two treatment groups on the morning of surgery. Forty patients will be randomized to receive a bodyweight-adjusted dose of 1mcg/kg of palonosetron (group I - GI) and another forty patients will receive a fix dose of 75 μg of palonosetron (group II - GII). Each study drug will be mixed with saline to a total volume of 10 ml in an unlabelled syringe and will be intravenously administered just prior to induction of anesthesia. All patients, surgeons, anesthesiologists involved in the study will be blinded to group allocation to maintain the double-blind conditions.

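### The protocol's listed tests give no arm-adjusted estimate for the genotype association; stratifying by randomised dose arm would recover a few points of power at almost no cost

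*Protocol*

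**What the plan says.** Protocol, Methods, gives the secondary outcome as the frequency of 5-HT3 receptor polymorphisms and "their correlation with the antiemetic effect and adverse effects". On the laboratory side, "a polymerase chain reaction (PCR) will be performed for analysis of single nucleotide polymorphisms". The number of polymorphisms, their expected frequency and the genotype coding are not given.

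The statistical paragraph of the same section names these methods:

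- for continuous data: "Patient characteristics and intra- and post-operative variables will be analysed by Unpaired" t-test;
- for categorical data: "Proportions will be compared using" chi-square or Fisher's exact test;
- a Wilcoxon test, but only as a check of normality: "The Wilcoxon signed rank 2x2 test will be use to ensure that data will be normally distributed".

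No stratified test, regression model or other arm-adjusted method appears, and no test is assigned specifically to the genotype aim.

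On allocation, forty patients receive the weight-adjusted dose and "another forty patients will receive a fix dose of 75" mcg. The hypothesis under Aims & Objectives is that the weight-adjusted regimen prevents nausea and vomiting better.

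**The concern.** The genotype question is asked in a group made up of two randomised arms. By the trial's own hypothesis, arm is a determinant of the antiemetic outcome to which genotype will be related. If genotype is cross-tabulated with outcome over all 80 patients, the arm effect stays in the unexplained variation. Arm is recorded for every patient and balanced by design, so it can be used at no cost, yet nothing on the test list uses it to give one combined estimate.

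The stake is power and precision. The only sample size calculation is for the dose comparison, so the genotype analysis has whatever power 80 patients happen to provide, and a few points are worth keeping.

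**Working it through.** **1. Inputs.** From the protocol: 40 patients per arm, 80 in total; significance level 0.05, taken as two-sided. Assumed, because the protocol gives no figure: allele frequency 0.2 to 0.4, per-allele odds ratio 2 to 2.5 (or a dominant odds ratio of 3), and the arm odds ratio.

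**2. The plan's own figure.** None is stated for the genotype analysis. For the dose comparison, the protocol states 36 per group at power 0.8. Without event rates this can be neither reproduced nor refuted, but it shows what size of arm effect fits. Two pairs that return 36 (two-sided, no continuity correction):

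- 50% v 19%: odds ratio (0.19/0.81)/(0.50/0.50) = 0.23
- 45% v 15%: odds ratio (0.15/0.85)/(0.45/0.55) = 0.22

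An arm odds ratio of 0.22 is therefore in line with the sample size. An odds ratio of 1/3 (50% v 25%) is a weaker case.

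**3. Validity of pooled tests.** With no genotype effect and an arm odds ratio of 1/3, simulated trials of 80 gave rejection rates of 4.6% to 5.6% for the pooled chi-square on carriers, 3.2% to 4.1% for Fisher's test, and 4.6% to 5.1% for a t-test on allele count. Ignoring arm does not inflate type I error.

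**4. Power with and without arm.** Each row keeps the genotype coding fixed, so the difference is due to arm alone. The per-allele odds ratio is 2.5 throughout.

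| Allele frequency | Arm odds ratio | Coding | Without arm | With arm | Gain (points) |
|---|---|---|---|---|---|
| 0.2 | 1/3 | carrier | 50.5% | 53.5% | 3.0 |
| 0.2 | 1/3 | allele count | 55.4% | 58.1% | 2.7 |
| 0.4 | 1/3 | carrier | 59.1% | 61.4% | 2.3 |
| 0.4 | 1/3 | allele count | 71.0% | 73.6% | 2.6 |
| 0.3 | 1/3 | allele-count trend | 66% | 69% | 3 |
| 0.3 | 0.22 | allele-count trend | 61% | 66% | 5 |
| 0.4 | 1/8 (extreme) | carrier | 47.9% | 57.1% | 9.2 |
| 0.4 | 1/8 (extreme) | allele count | 59.4% | 68.8% | 9.4 |

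The rows at allele frequency 0.3 come from 4,000 simulated trials with an assumed 50% baseline risk. The others come from 2,500 each. "Without arm" is the chi-square test for carriers and the unadjusted logistic or trend test for allele count. With no arm effect, stratifying costs less than 1 point.

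**5. Precision.** Assume 30% carriers, so 24 v 56, and an arm difference of 30 points around an average event rate of 35%.

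- SE of the difference in arm share: sqrt(0.25 × (1/24 + 1/56)) = 0.122
- Contribution of arm to the carrier risk difference: 0.122 × 0.30 = 0.037
- Total SE of the carrier risk difference: sqrt(0.35 × 0.65 × (1/24 + 1/56)) = 0.116
- Share of variance due to arm: 0.037² / 0.116² = about 10%
- Narrowing of the interval if arm is removed: 1 − sqrt(1 − 0.10) = about 5%

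**6. Does the genotype coding matter?** Yes, but the right choice depends on a genetic model that the protocol does not give. At arm odds ratio 1/3, allele count beats the chi-square on carriers by about 2 to 12 points when the effect is additive. When the effect is dominant it loses about 4 to 13 points (59.1% v 55.2% at allele frequency 0.2; 59.3% v 46.7% at 0.4).

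**The case against.** The strongest reply is that the protocol assigns no test to the genotype aim. It does not say that the arms will be pooled, and the model for a secondary association can properly sit in a statistical analysis plan, which is not at hand. That stands as a limit: the point rests on a general test list. It does not remove the point, because the protocol does set out its methods and none of them gives a combined arm-adjusted result.

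A reader might infer more than the document supports:

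- *That the listed tests cannot use allele count.* They can. A t-test of allele count between patients with and without the event has 72% power at allele frequency 0.4 and 54% at 0.2, against 71% and 55% for an unadjusted allele-count logistic model.
- *That the listed tests cannot hold arm constant at all.* They can be run within each arm, but that gives two separate results on 40 patients each and no combined estimate.
- *That chance imbalance of genotype between arms biases the result.* Arm is randomised and so independent of genotype. The imbalance is ordinary sampling error, already included in the SE of 0.116 above.
- *That the plan commits to a two-degree-of-freedom chi-square on three genotypes.* Nothing in the protocol says so, so the power lost by such a test cannot be charged to it.

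**Conclusion.** The point holds in a limited form. For a stated secondary outcome, the protocol lists no method that gives a combined genotype estimate adjusted for the randomised arm, although the trial expects the arms to differ on that outcome. Pooled analysis is valid but slightly inefficient. The loss is about 2 to 5 points of power for arm odds ratios from 1/3 to 0.22, about 9 points only at an extreme 1/8, and essentially nothing if the arms do not differ. The last case may well apply to adverse effects, on which the protocol states no arm hypothesis.

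All these sizes rest on assumed allele frequencies, genotype effects and event rates. Adjusting for arm does not make the genotype analysis well powered: most of the scenarios tabulated stay below 70%, and none reaches 80%. It is a free improvement to a secondary objective and leaves the trial's main conclusion untouched.

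**What to change.** Add one sentence to the statistical paragraph of Methods, or to the statistical analysis plan. It should say that each association between genotype and outcome will be tested and estimated with stratification by randomised dose arm (Mantel-Haenszel, or logistic regression with arm as a term), using one genotype coding chosen before the data are seen, and reported as an arm-adjusted odds ratio with a 95% confidence interval. The coding should be the investigators' choice on biological grounds. Additive 0/1/2 scoring should not be imposed, since it gains or loses power according to the true genetic model.

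The cost is a line of text and no new data. The power cost is below 1 point if the arms turn out not to differ. The sponsor should confirm that the named software runs the chosen stratified method, or name one that does.

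### The named normality check is a test of location, and the t-test then fixed for numeric post-operative outcomes, including the count of emetic episodes, has no rank-based or count-data alternative

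*Protocol*

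**What the plan says.** The statistical paragraph at the end of Methods has three relevant sentences. The first sets the check: "The Wilcoxon signed rank 2x2 test will be use to ensure that data will be normally distributed". The second sets the test for numeric data: "Patient characteristics and intra- and post-operative variables will be analysed by Unpaired Student´s t-test". The third covers binary data: "Proportions will be compared using x^2^ square or Fisher’s exact test". Significance is set at 0.05 without stating sidedness. No rank-based or count-data method appears, and nothing says what follows if the check fails.

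One of the outcomes is a count: "The primary outcome measure will include the number of emetic episodes, the incidence of nausea, the need for rescue antiemetics". The Abstract/Summary says the same, and Aims & Objectives lists episode frequencies by period among the primary objectives, for example "To determine the frequency of individual episodes of vomiting in the periods of 1, 6, 24 and 48 hours postoperatively". Other primary outcomes are binary: incidence of nausea, need for rescue, and complete antiemetic response.

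**The concern.** The signed-rank test compares paired differences, or one sample, with a fixed centre. It assumes symmetry and asks where the centre lies; it does not ask whether the data are normal. It has no 2x2 form, and no test can make data normal. The sentence therefore cannot be carried out as intended.

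The t-test follows whatever the check shows. For variables such as weight that is reasonable. For episode counts after prophylaxis, one expects many patients with none and a few with several. A difference in means then leans on those few patients, which can cost power and describes the typical patient poorly. If the analyst notices this only after seeing the data, any replacement test becomes a post hoc choice on a primary outcome.

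**Working it through.** **Plan's own figure.** The documents give no expected episode rate, count distribution or share of zeros. The 36 per group in Methods cannot be reproduced, because no rates, difference or SD accompany it. It can only be inverted. With two-sided alpha 0.05, power 0.8, no continuity correction and rates of 50% and 19%, n = [1.96 x sqrt(2 x 0.345 x 0.655) + 0.8416 x sqrt(0.25 + 0.1539)]^2 / 0.31^2 = (1.318 + 0.535)^2 / 0.0961 = 35.7, so 36. A contrast of 50% versus 20% is therefore close to one that the planned size would suit. It is an assumption, not a figure from the protocol.

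**Step 1: the signed-rank test as a normality check.** Take 40 positive values and a null of zero. Every signed rank is positive, so the exact two-sided p is 2 / 2^40 = 1.8e-12, whatever the shape. Simulated rejection rates at n = 40 and the 5% level (3000 samples each) were:

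| Data | Signed-rank (null 0) | Shapiro-Wilk |
|---|---|---|
| Normal, mean 0 | 4.8% | 5.1% |
| Normal, mean 90, SD 12 | 100% | 4.8% |
| t with 2 df, centred at 0 | 5.1% | 79% |
| Symmetric bimodal, centred at 0 | 5.5% | 100% |
| Uniform, centred at 0 | 4.5% | 58% |

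The check rejects normal data that lie away from the null and passes grossly non-normal symmetric data that lie on it.

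**Step 2: the t-test on episode counts.** Assume 40 per arm, any episode in 50% versus 20% of patients, and a given distribution of counts among those affected. The size of the t-test signal is the difference in means divided by its standard error; approximate power is Phi(ratio - 1.99).

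- One episode each: means 0.5 and 0.2, variances 0.25 and 0.16. Ratio = 0.3 / sqrt(0.41/40) = 2.96; power about 83%.
- Geometric, mean 2 (second moment 6): means 1.0 and 0.4, variances 0.5 x 6 - 1 = 2.00 and 0.2 x 6 - 0.16 = 1.04. Ratio = 0.6 / sqrt(3.04/40) = 2.18; power about 57%.
- Geometric, mean 3 (second moment 15): means 1.5 and 0.6, variances 5.25 and 2.64. Ratio = 0.9 / sqrt(7.89/40) = 2.03; power about 51%.

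Simulation, which does not rely on this normal approximation, gives:

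| Counts among affected patients | t-test | Rank-sum |
|---|---|---|
| One episode each | 82% | 82% |
| 1 + Poisson(0.5) | 72% | 80% |
| 1 + Poisson(1) | 69% | 80% |
| Geometric, mean 2 | 59 to 62% | 79 to 80% |
| Geometric, mean 3 | 55% | 79% |

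The rank-sum test stays near 80% because it depends mainly on who has any episode. With geometric counts (mean 2) and other rates, t-test versus rank-sum power is 61% versus 78% (40% versus 13% affected) and 69% versus 84% (30% versus 6%).

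**Step 3: the case that favours the t-test.** If the drug only scales a negative-binomial mean from 0.8 to 0.4 (dispersion k = 0.4), the share with no episode is (0.4/1.2)^0.4 = 64% versus (0.4/0.8)^0.4 = 76%. The contrast in patients affected is then small. Power is about 28% for the t-test and 23% for the rank-sum test.

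**Step 4: type I error.** With equal rates in both arms, the t-test rejects in roughly 4 to 6% of trials across the settings tried.

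**The case against.** The check carries no decision rule, so its failure changes no stated test and no p-value. That is true of the plan as written. It also means that a correctly chosen normality test would lead nowhere, which is why the missing alternative matters.

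The 100% rejection assumes a null of zero, and the protocol names no null value. This is fair, but the rows centred on the null show that a better placed value does not help: non-normal symmetric data still pass about 95% of the time.

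The power loss depends on assumed counts. This stands: the gap runs from 0 to about 24 points at 50% versus 20%, and reverses under pure scaling.

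Three stronger readings are tempting, and the documents do not support them. A reader might infer that every post-operative variable goes to the t-test. It does not, because the next sentence sends proportions to chi-square or Fisher's exact test; that covers incidence of nausea, need for rescue and complete response. The concern is confined to numeric variables: episode counts and, if recorded as an amount, analgesic requirement. A reader might take it as established that the counts are mostly zeros; that is an expectation, and no section gives a rate. A reader might infer inflated false positives; the simulations show none of consequence.

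A statistical analysis plan, not available here, may give more detail. That does not remove the point, because the protocol states the wrong check and fixes the t-test rather than leaving either open.

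**Conclusion.** The concern holds in a limited form. That the signed-rank test cannot check normality is certain and rests on no assumed rate. That a t-test is fixed for a primary count outcome with no alternative is plain from the text, reading the number of emetic episodes in its natural sense as a count per patient. The consequence is moderate and conditional: at 40 per arm and 50% versus 20% affected, t-test power is about 55% to 82% against about 80% for the rank-sum test. The loss grows as counts among affected patients become more dispersed, and there is a gain of about 5 points for the t-test if the effect is a uniform scaling of the mean. The level of the test is not threatened, and the binary primary outcomes have suitable tests. This should be fixed before analysis, but it does not undermine the trial.

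**What to change.** Delete the sentence on the signed-rank test. Replace the t-test sentence with wording to this effect: roughly symmetric continuous variables, such as weight or duration of surgery, will be compared by the unpaired t-test; episode counts and other clearly skewed numeric variables will be compared by the Wilcoxon rank-sum (Mann-Whitney) test, naming in advance which variables fall in each class. Leave the sentence on proportions as it is.

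Report an effect measure that matches the rank-sum test, for example the probability that a patient in one arm fares better than a patient in the other (ties counted as one half) with a 95% CI. A median difference would not serve: with 40% versus 13% affected and geometric counts, it was exactly 0 in 87% of simulated trials.

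The cost is two sentences. The one downside is slightly lower power, 28% falling to 23% in the example above, if the drug merely scales the mean count.
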